### Stopping rules

As the planned intervention does not introduce any specific therapeutic changes but focuses at intensifying the doctor-patient relation and over-thinking of therapeutic aims negative effects are very unlikely. However, the following stopping rule will be implemented and monitoring will cover these events at group level:

• if the average rate of hospital admissions increases more than 30% in any one group.

### Sample size/power calculations

For the sample size estimation of both endpoints an α=0.025 is assumed in order to adjust for multiple testing. The sample size calculation is based on preliminary analyses of the baseline assessment of the MultiCare Cohort study, which used the same inclusion criteria that are scheduled for this trial and also recruited patients via GP surgeries. In the MultiCare Cohort study patients averagely used 7.26 ± 3.5 medications (Median 7). We expect a mean reduction of 1.5 drugs per patient in the intervention group (difference baseline – follow-up) and no change (mean reduction 0) in the number of drugs in the control group (effect-size: 0.429). A common standard deviation of 3.5 drugs is assumed. Based on the data of the MultiCare Cohort study the intracluster correlation is ρ=0.14 and a minimum of 10 patients per GP are targeted. Under these assumptions and with α=0.025 and a power of 80% totally 48 GPs (475 patients) are necessary to detect the expected difference (2-sided t-test for equal variances). Given a drop-out rate of 20%, 594 patients (and 60 GP surgeries) are needed altogether. The dropout rates in other multicenter studies of the principal investigators are comparable (e.g. AgeCoDe: 16% within 1.5 years).

Regarding the other primary endpoint it is assumed that health related quality of life will not be inferior in the intervention group compared with the control group at the end of the intervention. On the instrument used (EQ-5D value set UK [20]) -0.59 till 1.0 points can be achieved. At the baseline assessment of the MultiCare Cohort study patients scored 0.68 ± 0.30 points. For testing non-inferiority it is assumed that the mean score of the intervention group at the end of the intervention is at most half a standard deviation (i.e. 0.15 points) less than that of the control group. Given a standard deviation of 0.30, an α=0.025, a power of 80%, an intra-cluster correlation of ρ=0.14, 128 patients are needed (1-sided test). Considering a design effect of 2.26 (minimum of 10 patients per GP) and a dropout rate of 20% we would need 362 patients altogether. As this number of patients is smaller than that for the other primary endpoint, the inclusion of 600 patients will be sufficient also for this health related quality of life endpoint. Statistical analyses will be on the intention to treat basis.

### Statistical analyses

Because of the cluster randomisation hierarchic multi-level models with GP as random effect (e.g. mixed model analysis of variance) will be applied for the statistical analyses of primary and secondary endpoints. Possible baseline imbalances and confounding variables will be controlled by adjustment. The data will be analysed according to the intention-to-treat principle. Because of the two primary endpoints Bonferroni correction will be applied to adjust for multiple comparisons.

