### Study hypotheses

We assume that the number of pharmaceutical agents taken by the patient can be reduced in the intervention group. We will compare the change in medication intake between baseline and follow-up in the intervention and control group. We expect that the mean difference between the changes in both groups will be at least 1.5 drugs less in the intervention group. A minimum difference of 0.5 drugs between both groups is defined as clinically relevant.

It is assumed that a reduction of medications used will not impair quality of life. We will compare the change in health related quality of life between baseline and follow-up in the intervention and control group. We expect that the mean change in the intervention group will not be statistically significantly inferior to the mean change in the control group.

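### Baseline value of each primary outcome is not fixed as a covariate, and the SD of 3.5 drugs describes the level, not the change that is to be compared

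*Protocol article*

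**What the plan says.** Under Study hypotheses, both primary outcomes are compared as change: "We will compare the change in medication intake between baseline and follow-up in the intervention and control group", and for EQ-5D "We will compare the change in health related quality of life between baseline and follow-up in the intervention and control group".

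Under Statistical analyses, the model is a multi-level model with GP as random effect, with mixed-model analysis of variance as an example. On covariates the section says "Possible baseline imbalances and confounding variables will be controlled by adjustment". It names neither the baseline value of the outcome nor any confounder.

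Under Sample size/power calculations, the effect is on the change scale: "We expect a mean reduction of 1.5 drugs per patient in the intervention group (difference baseline – follow-up"), against no change in the control group. The SD comes from a single time point: "The sample size calculation is based on preliminary analyses of the baseline assessment of the MultiCare Cohort study", where drug use averaged 7.26 with SD 3.5. The calculation then states "A common standard deviation of 3.5 drugs is assumed". The ICC of 0.14 is from the same cohort. No SD of change and no baseline to follow-up correlation is given.

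**The concern.** There are two linked problems.

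1. **The model.** Both primary outcomes are measured at baseline, so the baseline value is available as a covariate for every enrolled patient. Wording that ties adjustment to possible imbalances leaves open whether it enters the model, and that could be decided after the data are seen. The choice affects both the precision and the estimate itself.
2. **The SD.** The comparison is of change, but 3.5 is the spread of drug counts between patients at one visit. The SD of change depends on how strongly baseline and follow-up counts correlate. Without that correlation, the standardised effect of 0.429 and the 80% power are not tied to the comparison that the article describes.

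**Working it through.** **Inputs from the article.** Difference 1.5 drugs; SD 3.5; two-sided α = 0.025; power 80%; ICC 0.14; 10 patients per GP; 20% drop-out; 600 patients to be included. Equal allocation is assumed. The correlation r is not given, so a range is shown.

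**Reproducing the stated figures.**
- Effect size: 1.5/3.5 = 0.429. A two-sample t-test needs 105 per arm, 210 in total.
- Design effect: 1 + 9 × 0.14 = 2.26. Then 210 × 2.26 = 474.6, so 475.
- Drop-out: 475/0.8 = 593.75, so 594.

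The arithmetic is correct, and it uses the cross-sectional SD as the SD of the change.

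**SD under each analysis**, assuming equal variances at baseline and follow-up:
- Unadjusted change: 3.5 × √(2(1−r)). This equals 3.5 only when 2(1−r) = 1, that is at r = 0.5.
- Baseline-adjusted (ANCOVA): 3.5 × √(1−r²). This is never above 3.5.
- Variance ratio, change to ANCOVA: 2(1−r)/(1−r²) = 2/(1+r).

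**Results for 1.5 drugs**, with design effect 2.26 throughout. N is before drop-out, from the t-test. Power at 475 patients uses the normal approximation.

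| r | SD change | SD ANCOVA | Variance ratio | N change | N ANCOVA | Power change | Power ANCOVA |
|---|---|---|---|---|---|---|---|
| 0.3 | 4.14 | 3.34 | 1.54 | 665 | 434 | 65.0% | 84.5% |
| 0.4 | 3.83 | 3.21 | 1.43 | 570 | 403 | 72.4% | 87.5% |
| 0.5 | 3.50 | 3.03 | 1.33 | 475 | 358 | 80.7% | 91.1% |
| 0.6 | 3.13 | 2.80 | 1.25 | 385 | 308 | 89.1% | 95.0% |
| 0.7 | 2.71 | 2.50 | 1.18 | 290 | 249 | 96.2% | 98.3% |

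**Detectable difference at 80% power.** 600 × 0.8 = 480 completers, and 480/2.26 = 212.4 effective patients. The difference is (2.241 + 0.842) × SD × √(4/212.4). Change versus ANCOVA gives 1.48 versus 1.28 drugs at r = 0.5, and 1.15 versus 1.06 at r = 0.7.

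**What the choice of model can do to the estimate.** The standard error of the between-arm difference at baseline is 3.5 × √(4/212.4) = 0.48 drugs. The unadjusted change estimate and the ANCOVA estimate differ by about (1−r) times the baseline difference. For a one-standard-error imbalance that is 0.24 drugs at r = 0.5 and 0.14 at r = 0.7, against the article's minimum relevant difference of 0.5 drugs.

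**EQ-5D.** A one-sided t-test with SD 0.30, margin 0.15 and α = 0.025 needs 64 per arm, 128 in total; 128 × 2.26/0.8 = 361.6, so 362 as stated. Even for an unadjusted change score at r = 0.3, the normal approximation gives 497 patients after drop-out, still below 600.

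**The case against.** The strongest reply is that the article does not commit to an unadjusted change score. Comparing change does not rule out baseline adjustment: with the baseline value in the model, change and follow-up as response give the same treatment estimate and standard error. The adjustment sentence also covers confounding variables, not only imbalances, and it states no test or trigger for selecting covariates. A full covariate list may properly stand in an analysis plan that is not shown. All of this stands. A reader might infer that precision is thrown away on both primaries. The text does not support that, because the loss arises only if baseline is omitted, which is nowhere stated.

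A reader might also infer that the trial is underpowered. The text does not support that either. Power falls short of 80% only for an unadjusted change score with r below 0.5; above 0.5, an SD of 3.5 is conservative. The article gives its source openly and calls the SD assumed.

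For EQ-5D, the sample size section sets the margin on the score at the end of the intervention, and a cross-sectional SD suits that target. The SD point reaches EQ-5D only through the change wording under Study hypotheses.

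Finally, the figures above apply the ICC of 0.14 to change scores and to ANCOVA residuals. The ICC for either could be higher or lower, so this too is an assumption.

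What remains is that the one covariate that matters most is left open by wording that links adjustment to possible imbalance, and that the SD is not matched to the stated contrast.

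**Conclusion.** The point holds as a matter of pre-specification and of an unsupported input. It is not an arithmetic error. Leaving baseline out would inflate the variance by a factor of 1.33 at r = 0.5 or 1.18 at r = 0.7, and whether it is included could move the medication estimate by roughly 0.1 to 0.2 drugs under an ordinary chance imbalance. The stated 80% power is correct for an unadjusted change score only near r = 0.5.

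These sizes rest on equal variances at both visits, equal allocation, an ICC of 0.14 carried over to change and residuals, and values of r that are assumed. Baseline adjustment would not bring the detectable difference near 0.5 drugs; its value lies in a fixed model and in precision gained at no cost.

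**What to change.** - **Statistical analyses.** For both primaries, pre-specify a mixed model with a GP random intercept, treatment arm, and the baseline value of the same outcome as a covariate, whatever imbalance is observed. Either follow-up or change may be the response. Move adjustment for observed imbalances to sensitivity analyses. Study centre may be added as a covariate but need not be.
- **Sample size/power calculations.** Label 3.5 as the SD of the level. State that with baseline adjustment the residual SD is 3.5 × √(1−r²), at most 3.5, so that 475 patients give about 80% power or more at the assumed ICC. Say that 0.14 is an assumption for the adjusted outcome.

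The cost is a few sentences of analysis wording and a restated power paragraph. No further data or patients are needed.

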## Abstract

**Background:**

This study investigates the efficacy of a complex multifaceted intervention aiming at increasing the quality of care of GPs for patients with multimorbidity. In its core, the intervention aims at enhancing the doctor-patient-dialogue and identifying the patient’s agenda and needs. Also, a medication check is embedded. Our primary hypothesis is that a more patient-centred communication will reduce the number of active pharmaceuticals taken without impairing the patients’ quality of life. Secondary hypotheses include a better knowledge of GPs about their patients’ medication, a higher patient satisfaction and a more effective and/or efficient health care utilization.

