It is also not known which specific aspects of care for patients with multimorbidity by German GPs can and should be optimized within the available resources and which of them have a realistic chance to show sustained effects. What we do know is that German GPs see their patients very often for a short time at each visit. German doctors in ambulatory care see 243–309 patients a week, much more than e.g. UK doctors with 154–205 contacts. It is understood that this number includes a number of patients without face to face contact (e.g. repeated drug prescriptions [7]). This high contact frequency results in a contact duration of only 7.6-7.8 minutes per patient [8,9]. These and other research results [10] suggest that the elements of chronic illness care mentioned above may insufficiently be put into practice as they afford a considerable amount of communication time. Routine doctor-patient consultation is usually determined by real and by perceived time-constraints and a by doctor-centred consultation-style.

The concept of “narrative based medicine” was established by Greenhalgh et al. [11] in order to stop this negative development. The concept assumes that patient narratives of illness can provide a framework for approaching a patient’s problems holistically and may uncover diagnostic and therapeutic options. This concept has not yet been linked to the Chronic Care Model.

The MultiCare AGENDA study investigates the efficacy of a complex multifaceted intervention aiming at increasing the quality of care of GPs for patients with multimorbidity. When treating patients with multimorbidity it is crucial to prioritize and set goals. Only if the patient perspective is known, the main focus of treatment can be defined. Therefore in its core, the intervention aims at enhancing the doctor-patient-dialogue and identifying the patient’s agenda and needs, including the need for social support. Also, a medication check is embedded in this intensified dialogue. Our primary hypothesis is that a more patient-centred communication can disclose the main focus of treatment of the patient which often will have implications for medication use. Therefore the primary hypothesis is that the patient-centered communication in the form of narrative based medicine leads to a reduction of the number of medication taken without reducing health related quality of life.

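### The primary hypothesis requires both endpoints, but alpha is split by Bonferroni as for alternative endpoints, no both-must-succeed rule is given, and power for the joint claim is about 76% rather than 80%

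*Protocol article*

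**What the plan says.** The hypothesis is joint wherever it is stated in full. In the Background section of the protocol article, narrative-based communication "leads to a reduction of the number of medication taken without reducing health related quality of life". The abstract says that it "will reduce the number of active pharmaceuticals taken without impairing" quality of life, and the Conclusions repeat the same pairing. The Study hypotheses section takes the two parts in turn: superiority on the change in drug number, then quality of life not inferior, with the second part framed as a consequence of taking fewer drugs.

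The testing rule is in two places. Under Sample size/power calculations: "For the sample size estimation of both endpoints an α=0.025 is assumed in order to adjust for multiple testing". Under Statistical analyses: "Because of the two primary endpoints Bonferroni correction will be applied to adjust for multiple comparisons".

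Each endpoint is sized on its own at 80% power. The article does not say whether one endpoint or both must succeed for a positive trial, and it gives no power for the two together.

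**The concern.** The multiplicity rule should follow from the claim. If success means at least one of two endpoints, there are two chances of a false positive, and Bonferroni controls them. If success means both, the test is an intersection-union test: each part is tested at full level, and the joint error rate cannot exceed that level. The article states the second kind of claim and uses the correction for the first.

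Two things are at stake. The first is how the result will be judged. Without a stated rule, a trial that meets only one endpoint can be read either way after the results are known. Non-inferiority on EQ-5D carries little information here unless drug number falls, because an inert intervention would be expected to meet it. Conversely, fewer drugs with an unacceptable loss of quality of life would meet one primary endpoint while contradicting the hypothesis. The second is power: a figure given per endpoint overstates the chance of confirming a hypothesis that needs both.

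**Working it through.** **Inputs**, all from Sample size/power calculations unless marked:
- Drug number: "We expect a mean reduction of 1.5 drugs per patient in the intervention group" against no change in controls; "A common standard deviation of 3.5 drugs is assumed". Standardised effect 1.5/3.5 = 0.429.
- Drug number, level and size: "with α=0.025 and a power of 80% totally 48 GPs (475 patients) are necessary to detect the expected difference (2-sided t-test for equal variances".
- Clustering: "the intracluster correlation is ρ=0.14 and a minimum of 10 patients per GP are targeted". Design effect = 1 + (10 − 1) × 0.14 = 2.26.
- EQ-5D: margin 0.15, standard deviation 0.30, one-sided 0.025, power 80%. Standardised margin 0.15/0.30 = 0.5.
- Dropout 20%.
- Assumed: 1:1 allocation and a true EQ-5D difference of 0. Neither is stated, but together they reproduce the plan's figures.

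**1. Reproducing the plan's figures** (two-sample noncentral t)
- Drug number, two-sided 0.025, 80%: 105 per arm; 210 × 2.26 = 474.6, so 475; 475/0.8 = 593.75, so 594. Matches.
- EQ-5D, one-sided 0.025, 80%: 64 per arm, 128 in total; 128 × 2.26/0.8 = 361.6, so 362. Matches.

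**2. Power of each test at 475 evaluable patients**

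Effective sample = 475/2.26 = 210.2, or 105.1 per arm. Noncentrality = standardised effect × √(105.1/2), about 3.11 for drug number and 3.62 for EQ-5D.

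| Test | Level | Power |
|---|---|---|
| Drug number, as planned | two-sided 0.025 | 80.1% |
| Drug number, no split | two-sided 0.05 | 87.1% |
| EQ-5D non-inferiority | one-sided 0.025 | 95.0% |

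The EQ-5D figure is computed at a true difference of 0. It is therefore also the probability that an intervention with no effect shows non-inferiority.

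**3. Power for both endpoints together**

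Under independence, joint power = P1 × P2. Whatever the dependence, it lies between P1 + P2 − 1 and the smaller of P1 and P2. The correlation between the two tests is not given, so the range is shown.

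- As planned: 0.8013 × 0.9503 = 0.7615, about 76%. Bounds: 0.8013 + 0.9503 − 1 = 0.7516 to 0.8013, so 75% to 80%. For correlations from −0.5 to 0.5 it is 75.2% to 78.1%.
- Both required, no split: 0.8712 × 0.9503 = 0.8279, about 83%. Bounds: 0.8712 + 0.9503 − 1 = 0.8215 to 0.8712, so 82% to 87%.

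With 600 enrolled and 480 evaluable, the independence figures are 0.8059 × 0.9522 = 76.7% as planned and 0.8747 × 0.9522 = 83.3% without the split.

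**4. Patients needed for 80% joint power (independence)**
- With the split kept (two-sided 0.025 and one-sided 0.025): about 511 evaluable; 511/0.8 is about 639 enrolled, more than the 600 planned.
- Without the split (two-sided 0.05 and one-sided 0.025): about 450 evaluable, about 562 enrolled, fewer than planned.

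**The case against.** The strongest defence is that Bonferroni does no harm to the joint claim. If both endpoints must succeed, testing each at 0.025 is conservative and cannot inflate type I error. That stands: on this reading the cost is efficiency, not validity.

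A reader might go further and infer that the plan lets quality of life alone count as success, so that an inert programme would almost always be called positive. The article does not support this. It nowhere says that one endpoint is enough, and its joint wording points the other way. If the intervention does nothing, non-inferiority is also true, so showing it is a correct finding; it misleads only if reported as trial success. The either-endpoint reading is what Bonferroni ordinarily implies, but here it is an inference.

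A reader might also infer that the sample size is wrong. It is not: 475/594 and 128/362 both reproduce, and the article claims 80% per endpoint, never jointly. The joint shortfall is about 4 points under independence.

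It can also be said that two separate confirmatory claims would justify splitting alpha, and that an article may leave the success rule to a fuller document. Silence on the rule would indeed be no finding. But the split is an affirmative choice, made in two sections and built into the sample size, and it does not fit the hypothesis as worded. A later rule requiring both endpoints would make those statements redundant.

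**Conclusion.** The mismatch is real and unresolved in the article: a joint hypothesis is paired with the correction for alternative endpoints. If both endpoints are required, the plan is valid but has about 76% power for its hypothesis (75% to 80% over all dependence, reaching 80% only at the extreme upper bound). Full-level testing of both would give about 83% (82% to 87%). If either sufficed, the roughly 95% chance of EQ-5D non-inferiority under no effect would make a positive primary endpoint nearly uninformative about the hypothesis.

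These figures rest on the plan's own effect, standard deviations, intracluster correlation and margin, on 475 evaluable patients, on 1:1 allocation, and on a true EQ-5D difference of 0. The power loss is modest; the stronger reason to act is that the decision rule should be fixed before results are seen. It should be fixed, but it is not a flaw that undermines the trial.

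**What to change.** - State that the primary claim requires both superiority on drug number at two-sided 5% and non-inferiority on EQ-5D at one-sided 2.5%. The EQ-5D level is the one already used in the sample size section.
- Remove the Bonferroni sentence under Statistical analyses and the multiple-testing clause under Sample size/power calculations.
- State that EQ-5D non-inferiority alone is not a positive trial.
- Report joint power of about 83% under independence (82% to 87% over all dependence) at 475 evaluable patients.

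The cost is wording and one restated power figure; no extra patients are needed. The real downside is that success on a single endpoint can no longer be claimed. If the investigators do want two separate claims, they should keep the split and reword the primary hypothesis to match.

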### Quality assurance and safety

Reliability trainings and checks will be performed before starting the study and subsequently yearly with the whole staff involved in interviewing and data collection.

IT, data management and quality assurance will be provided by the Institute of Biometry, Hannover Medical School. Quality assurance consists of procedures for prevention of insufficient data quality, detection of inaccurate or incomplete data and action to improve data quality, e.g. user training sessions, automatic plausibility and integrity checks within the remote data entry system and data error reports for the local centres. In addition the centres will regularly receive feedback by quality reports. Two monitoring and training visits per centre are planned: one at the beginning of the trial and one after finishing the recruitment phase. In addition a random sample of paper questionnaires (5%) will be compared with the data entries in the database. Adverse events will be monitored and reported.

